#### Difference in differences

To quantify an overall effect on length of hospital stay after implementing the “In-HospiTOOL”, we fit a patient-level multivariate linear regression model. It will include lengths of hospital stay of “control” hospitals, all risk adjusters listed above in the manuscript, and a time variable for study weeks. The dependent variable will be length of hospital stay (days in hospital). We will test for interaction between the intervention period and the intervention population and will assess whether there is a difference in the change (slope) in length of hospital stay over time between the two study populations. The intervention and control groups will have different baseline characteristics, however both groups will be exposed to similar alterations in outcomes over time without the interventional program.

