## Methods/design

### Aim and study design

The “In-HospiTOOL” study is a quasi-experimental investigator-initiated, multicenter effectiveness trial investigating the effects of a new patient in-hospital management tool to improve length of hospital stay and other outcomes using an ITS model. The overall 18-month study time is divided in a 6-month observational phase, a 6-month implementation phase, and a 6-month intervention phase.

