### Setting, study sites and characteristics of participants

The multicenter trial includes seven secondary and tertiary care hospitals within Northern Switzerland. This allows to collect representative nation-wide patient-oriented data from polymorbid patients. All senior executive leaders have reassured full support for an optimal implementation of the “In-HospiTOOL” in their hospitals. Upon hospital admission, consecutive adult (age ≥ 18 years), polymorbid (> 1 diagnose) medical inpatients will be included in our study. Except for non-medical and non-adult patients there will be no exclusion criteria.

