### Statistical analysis plan and sample size

The primary analysis population includes all consecutively recruited patients following an intention-to treat (ITT) principle. The number of patients lost to follow-up will be minimized by every effort. The per-protocol (PP) population analysis will be prospectively defined to exclude patients in whom major protocol violations have occurred. Specifically, the following criteria will lead to exclusion from the PP population: major violation of study inclusion or study exclusion criteria, patients with missing information from the In-HospiTOOL forms, or missing follow-up interviews.

We will compare all endpoints between all three study phases in the overall ITT population, the PP population and within predefined subgroups as discussed below. We will analyze all endpoints in an adjusted manner for the main covariates such as age, gender, health care insurance, home of residence, main diagnosis, comorbidities, and study center. Regarding sample size considerations, we include consecutive patients in each hospital over a 6-month period for the observation, implementation, and the intervention period, respectively. Given the large number of patients per study site seen in routine (i.e. between 2`500 and 8`000 polymorbid medical inpatients) per year, we estimate to enroll approximately ~ 35′000 patients over 18 months of recruitment. This large amount of patient data will provide adequate power to investigate the effect of introducing a patient care tool in the overall medical hospitalized patient population and allow for subgroup analyses, as well as important post-hoc analyses.

We will perform two complementary, quasi-experimental analyses to estimate the effect of the intervention: difference in differences and ITS.

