#### Interrupted time series (ITS) model

We will analyze the trends in length of hospital stay from start of observation through the end of the intervention period (18 months). For this purpose, we will conduct an ITS as a sensitivity analysis. We will implement the ITS using generalized estimating equations (GEE), to examine linear trends in weekly, hospital-level, risk-adjusted length of hospital stays. ITS models will be tested for autocorrelation to control for seasonal trends using the Durbin-Watson statistics [25]. We will analyze the change in trend between all three time periods. This approach allows us to distinguish between a possible effect of the intervention and a difference from underlying trends facing both study groups and can also help to analyse whether the intervention effects will sustain over time. We will calculate weekly-adjusted length of hospital stay using linear GEE that includes all lengths of hospital stay from the control and intervention populations and all above mentioned risk factors. We will graph weekly length of hospital stay for all populations over time and use the estimated weekly means for control and intervention patients to assess for a weekly difference between the two groups. Finally, we explore whether the adjusted weekly length of hospital stay decreases in the intervention period and whether there will be an independent time trend effect induced by the intervention only [26].

To summarize, we will use four statistically hypothesis tests during each period: (i) Are there significant trends in length of hospital stay change during the period. (ii) Will the trend differ between the control and intervention populations (the interaction between time and control or intervention conditions) during the period. (iii) Will the trend during the intervention period differ from the trend during the observation period within all three conditions. (iiii) Will the magnitude of the altered trend between the intervention and the observation period differ between the three conditions (the interaction between the change in slope and intervention or control conditions). These models will also be implemented for the analyses of the secondary endpoints.

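### The main difference-in-differences model names no allowance for hospital-specific change between phases, with only seven intervention hospitals, and the power statement counts patients, not hospitals

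*Protocol article*

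**What the plan says.** All references are to the protocol article.

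- **Main effect model.** Under Difference in differences: "we fit a patient-level multivariate linear regression model". Its contents are described as follows: "It will include lengths of hospital stay of “control” hospitals, all risk adjusters listed above in the manuscript, and a time variable for study weeks". Further on, the effect is tested thus: "We will test for interaction between the intervention period and the intervention population".
- **Hospital in the model.** The adjusters listed under Statistical analysis plan and sample size end with "main diagnosis, comorbidities, and study center".
- **Units and timing.** Under Setting: "The multicenter trial includes seven secondary and tertiary care hospitals within Northern Switzerland". Under Aim and study design, the study is "divided in a 6-month observational phase, a 6-month implementation phase, and a 6-month intervention phase", with no separate timetable per hospital.
- **Correlation.** It is addressed only in the ITS section: "We will implement the ITS using generalized estimating equations (GEE), to examine linear trends in weekly, hospital-level, risk-adjusted length of hospital stays", plus a Durbin-Watson check for autocorrelation. That section calls the ITS a sensitivity analysis, which leaves difference in differences as the main estimate.
- **Power.** After an expected enrolment of about 35,000 patients, the text concludes: "This large amount of patient data will provide adequate power to investigate the effect of introducing a patient care tool". It gives no effect size, SD, intraclass correlation, significance level or power figure.
- **The clusters.** The limitations paragraph of the Discussion identifies hospitals as the clusters and says a cluster randomized trial would need many of them.

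**The concern.** Every patient in an intervention hospital changes exposure when the hospital changes phase. The interaction therefore compares seven hospital changes with the changes in control hospitals. It has to be judged against how much a hospital's mean stay moves between two six-month periods for reasons unrelated to the tool, such as staffing, bed policy or nursing-home capacity.

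A center term takes out what is constant in a hospital. It does not take out that movement. An ordinary patient-level regression measures uncertainty only from the spread between patients, and with about 1,667 patients per hospital and phase that spread averages out almost completely. What is left, hospital-specific drift, is the part that an ordinary standard error does not see.

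At stake is the primary conclusion that the tool shortens the stay. The ITS section extends the models to the secondary endpoints, so the same weakness carries over to them. The power statement has the same root: adding patients within seven hospitals does not reduce the variation between hospitals.

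**Working it through.** **The plan's own figure.** Seven sites at 2,500 to 8,000 patients per year for 1.5 years give 7 × 2,500 × 1.5 = 26,250 to 7 × 8,000 × 1.5 = 84,000. The stated 35,000 lies in that range. No power figure can be reproduced, since none is given.

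**Inputs from the article.** 35,000 patients, 3 phases, 7 hospitals. Hence n = 35,000/3 = 11,667 per phase and 11,667/7 = 1,667 per hospital and phase.

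**Assumed, not in the article.** Two-sided 5% level; stay SD σ of 6 or 8 days; equal phases and equal hospital sizes; control-side variance negligible; hospital-by-phase SD τ from 0 to 0.3 days, remaining after center terms. Equal sizes and negligible control variance both favour the plan's precision.

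**Formulas**, for intervention phase minus observation phase:

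- Naive SE = √(2σ²/n)
- SE with hospital drift = √(2σ²/n + 2τ²/7)
- False-positive rate with naive errors = 2 × P(Z > 1.96 × naive SE / SE with drift)
- Detectable difference at 80% power: noncentral t on 6 degrees of freedom (7 hospitals − 1)

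**Numbers put in.** For σ = 6: 2 × 36/11,667 = 0.00617, so the naive SE is 0.079 days. For σ = 8: 2 × 64/11,667 = 0.01097, naive SE 0.105. For τ = 0.2: 2 × 0.04/7 = 0.01143, so the SE is √(0.00617 + 0.01143) = 0.133 for σ = 6 and √(0.01097 + 0.01143) = 0.150 for σ = 8.

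| τ (days) | SE, σ = 6 / 8 | False positives at nominal 5% | Detectable difference (days) |
|---|---|---|---|
| 0 | 0.079 / 0.105 | 5% / 5% | 0.26 / 0.35 |
| 0.1 | 0.095 / 0.118 | 11% / 8% | 0.32 / 0.40 |
| 0.2 | 0.133 / 0.150 | 25% / 17% | 0.45 / 0.50 |
| 0.3 | 0.179 / 0.192 | 39% / 28% | 0.60 / 0.64 |

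Counting patients only, the detectable difference is (1.96 + 0.84) × naive SE = 0.22 / 0.29 days. The step from there to the first row comes from the t reference with 6 degrees of freedom alone; the rest of the increase comes from τ.

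A τ of 0.2 days is a residual intraclass correlation of only τ²/σ² = 0.04/36 = 0.0011, or 0.04/64 = 0.0006.

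**Check by simulation.** Hospital-period means were simulated with center effects removed (20,000 runs, σ = 7, 7 intervention hospitals against 7 or 100 control hospitals). The naive test rejected in about 5% of runs at an intraclass correlation of 0 and in 23% at 0.001. The number of control hospitals made almost no difference. A Welch test on the hospital changes rejected in 4.5 to 5.3% over all settings examined.

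**The case against.** The strongest reply is that the article names the unit of observation and the terms of the model, but no variance estimator. A patient-level regression with hospital-clustered or bootstrap errors fits the same sentence, and such detail may stand in a fuller plan. This is correct as far as it goes. A reader might infer that the plan declares patients independent, or that its standard errors are shown to be wrong. The text does not support either: it states no independence assumption and no standard error.

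Nor can the power statement be called false. Without a target effect and variances it is unsupported, and with a large effect or very little hospital drift the power could be sufficient. A staggered introduction, one hospital after another, should not be read in either: a single common schedule is described. The ITS text likewise names no particular GEE variance estimator, so there is no stated choice to criticise there, only a caution about few treated clusters.

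It is also fair that the design does not ignore the hospital level. Observation and intervention phases are season-matched, controls absorb shared trends, center is adjusted for, and the ITS works on weekly hospital-level data. But none of these removes change specific to one hospital between phases.

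Two things remain after these concessions. The article specifies its main model and test, and names a method for correlated data only for the sensitivity analysis. And its power argument counts patients whichever variance estimator is later chosen, although the limitations paragraph recognises hospitals as the clusters.

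**Conclusion.** The point holds in a conditional form. If the main model is fitted as written, with ordinary errors, its standard error is likely too small. How much depends on a quantity the article does not give. With no hospital-by-phase variation there is no problem; at 0.1 day the inflation is modest (8 to 11% instead of 5%); at 0.2 to 0.3 days it is serious (17 to 39%). These figures rest on the assumptions listed above: SD of 6 to 8 days, equal hospital sizes, negligible control variance.

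The claim of adequate power is unsupported. At a hospital-by-phase SD of 0.3 days, the difference detectable with seven hospitals is about 0.60 to 0.64 days, against the 0.22 to 0.29 days that patient numbers alone would suggest.

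This should be settled before the analysis, because the primary conclusion depends on this one test.

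**What to change.** - **Main analysis.** Keep the adjusted patient-level model for the point estimate. Take the confidence interval and p-value from the hospital level, by one method fixed in advance that is valid for few clusters. One option is to compare the seven risk-adjusted hospital changes with the changes in control hospitals; in the simulation above, a Welch test of this kind held its level. Another is permutation over placebo sets of seven control hospitals. Which one is chosen matters less than naming it beforehand.
- **ITS.** If robust GEE errors are used, add a small-sample correction with a t reference.
- **Power.** Replace the sentence with a detectable difference based on seven hospitals, over a stated range of hospital-by-phase SD, as in the table.

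**Cost.** No further patients are needed, only plan wording and some analysis work. The control data must carry a coded hospital identifier; the Control population section already lists study center among the adjusters, but whether the federal data will contain one for each control hospital should be confirmed. The downside is wider intervals and a less favourable power statement.

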#### Interrupted time series (ITS) model

We will analyze the trends in length of hospital stay from start of observation through the end of the intervention period (18 months). For this purpose, we will conduct an ITS as a sensitivity analysis. We will implement the ITS using generalized estimating equations (GEE), to examine linear trends in weekly, hospital-level, risk-adjusted length of hospital stays. ITS models will be tested for autocorrelation to control for seasonal trends using the Durbin-Watson statistics [25]. We will analyze the change in trend between all three time periods. This approach allows us to distinguish between a possible effect of the intervention and a difference from underlying trends facing both study groups and can also help to analyse whether the intervention effects will sustain over time. We will calculate weekly-adjusted length of hospital stay using linear GEE that includes all lengths of hospital stay from the control and intervention populations and all above mentioned risk factors. We will graph weekly length of hospital stay for all populations over time and use the estimated weekly means for control and intervention patients to assess for a weekly difference between the two groups. Finally, we explore whether the adjusted weekly length of hospital stay decreases in the intervention period and whether there will be an independent time trend effect induced by the intervention only [26].

To summarize, we will use four statistically hypothesis tests during each period: (i) Are there significant trends in length of hospital stay change during the period. (ii) Will the trend differ between the control and intervention populations (the interaction between time and control or intervention conditions) during the period. (iii) Will the trend during the intervention period differ from the trend during the observation period within all three conditions. (iiii) Will the magnitude of the altered trend between the intervention and the observation period differ between the three conditions (the interaction between the change in slope and intervention or control conditions). These models will also be implemented for the analyses of the secondary endpoints.

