### Data collection process

The study period is divided into three 6-month phases, whereas the observation and the intervention phase until the end of January 2019 are season-matched, interrupted by a run-in non-season-matched implementation phase. The period of “In-HospiTOOL” implementation in the participating hospitals will be devoted to technical implementation, training of involved study personnel, nurses, social workers, physicians, and pilot testing. We will collect data throughout all three study periods by using electronic medical records and will contact all patients 30 days after hospital admission by phone interview. Data from the structured phone interviews will be stored on a data base using the secuTrial© software (secuTrial®; interActive Systems GmbH, Berlin, Germany).

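### The time-series analysis relies on a Durbin-Watson test to control season, which it cannot do, while comparing phases of which one is not season-matched

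*Protocol article*

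**What the plan says.** Under Aim and study design, the 18 months are "divided in a 6-month observational phase, a 6-month implementation phase, and a 6-month intervention phase". Under Data collection process, "the observation and the intervention phase until the end of January 2019 are season-matched", and these two phases are "interrupted by a run-in non-season-matched implementation phase".

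Under Interrupted time series (ITS) model, generalized estimating equations (GEE) are used "to examine linear trends in weekly, hospital-level, risk-adjusted length of hospital stays". Season is addressed in one sentence: "ITS models will be tested for autocorrelation to control for seasonal trends using the Durbin-Watson statistics". The section continues: "We will analyze the change in trend between all three time periods". It then lists four tests:

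- (i) is there a trend within a period;
- (ii) does that trend differ between control and intervention populations;
- (iii) does the intervention-period trend differ from the observation-period trend;
- (iiii) does that change differ between the populations.

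The same models are to be used for the secondary endpoints. The section labels the ITS a sensitivity analysis.

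Under Statistical analysis plan and sample size: "We will compare all endpoints between all three study phases in the overall ITT population". The adjusters listed there, under Control population and under Independent variables are patient characteristics and study center. None is a month, quarter or season. The difference-in-differences (DiD) model has "a time variable for study weeks". For the control hospitals, Control population names one outcome, length of stay.

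**The concern.** The article names a tool for seasonality, and the tool cannot do that job. The Durbin-Watson statistic compares successive residuals. It estimates no seasonal effect, subtracts none, and is not aimed at an annual cycle. A straight line fitted to half a year can absorb much of an annual cycle, which leaves residuals that look clean. A passed test would then be read as evidence that season had been dealt with.

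This matters because each phase covers only half a year and the implementation phase falls in the other half of the calendar from its neighbours. A seasonal rise in one phase and fall in the next can appear as a change of trend when the tool is introduced. If the cycle peaks mid-phase, it appears as a difference in phase means instead.

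**Working it through.** The article gives no seasonal amplitude, peak week or weekly standard deviation, so there is no stated figure to reproduce. What follows is an illustration under assumptions.

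**Inputs from the article.** Three phases of 6 months, taken as 3 × 26 = 78 weeks. The last phase ends in January 2019, so the phases run roughly August–January, February–July and August–January (inferred). Time is linear within a phase.

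**Assumptions.** No tool effect, one uncontrolled series, and a stable annual cycle y(t) = A cos(2π(t − p)/52), where t is the study week from 0, p the peak week and A the amplitude.

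**Step 1: fitted slopes.** A separate least-squares line is fitted in each phase. Results for A = 0.2 days, with slopes in days per 26 weeks:

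| Peak week p | Observation | Implementation | Intervention | Implementation − observation | Intervention − observation |
|---|---|---|---|---|---|
| 0 (phase boundary) | −0.49 | +0.49 | −0.49 | +0.97 | 0 |
| 13 (mid-phase) | +0.03 | −0.03 | +0.03 | −0.06 | 0 |
| 24 | +0.48 | −0.48 | +0.48 | −0.96 | 0 |
| 26 (phase boundary) | +0.49 | −0.49 | +0.49 | −0.97 | 0 |

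At the exact midpoint, p = 12.5, the slopes are 0. The maximum agrees with the closed form for a half-year window: slope × 26 weeks = (24/π²)A = 2.43 × 0.2 = 0.486, and two slopes of opposite sign differ by 2 × 0.486 = 0.97. Everything scales with A, so at 0.4 days the range is about 0 to 1.94.

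**Step 2: phase means.** With a mid-phase peak the means are +(2/π)A and −(2/π)A. The gap is (4/π) × 0.2 ≈ 0.25 days between observation and implementation, and 0 between observation and intervention. The peak week therefore decides whether trend or level is contaminated.

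**Step 3: projected level.** Extending the observation line to the start of the intervention phase gives a false level difference of −4.86 × 0.2 = −0.97 days for p = 26, and +0.97 for p = 0. Season matching does not protect such a projection.

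**Step 4: would Durbin-Watson notice?** There were 2,000 simulated series per setting, with independent weekly noise of SD 0.3 days (assumed) and two-sided 5% slope tests. The 5% Durbin-Watson cut-off was simulated for the same design. Results for p = 24:

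| A (days) | False implementation − observation slope change | Durbin-Watson rejects |
|---|---|---|
| 0.1 | 39% | 4% |
| 0.2 | 91% | 6% |
| 0.3 | 99.8% | 6% |
| 0.5 | 100% | 9% |

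At A = 0.2 the intervention − observation slope change was significant in 5% of runs, as it should be. With p = 13 the false slope change stayed near 4–5%, while Durbin-Watson rejected in 7–52% across the same amplitudes. So the test is mostly silent where the slope bias is large, and speaks more often where that bias is small.

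**The case against.** The strongest reply is that the design already protects the contrasts that bear on the tool's effect, and much of it stands.

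- **Matched phases.** A reader might infer that the main before-and-after comparison is confounded by season. The article does not support that. Test (iii) sets intervention against observation, the season-matched pair, and the bias in that slope contrast is 0 for every peak week if the cycle is stable.
- **Concurrent controls.** Both models include control hospitals, and the Discussion says they are there to account for epidemiological variation. A season common to both groups cancels in tests (ii) and (iiii).
- **Rank.** The ITS is a sensitivity analysis. The overall effect on length of stay is quantified by the DiD, and test (i) is not itself a test of the tool.
- **DiD week term.** It is tempting to say that the DiD forces a linear week effect. The section says only that a time variable enters; week indicators are not ruled out.
- **Standard errors.** It is also tempting to say that they will be too small under autocorrelation. The ITS uses GEE, which is built for correlated data, and the working correlation may properly be left to the analysis plan.
- **Peak week.** The slope bias nearly vanishes for a mid-phase peak, so figures near 0.97 days are the worst case.

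The reply does not rescue the Durbin-Watson sentence. That sentence states a method for season that cannot do what it is said to do, so it is more than a detail left to another document. Nor does the reply cover the comparisons across all three phases, or the secondary endpoints for which no control outcome is described.

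**Conclusion.** The point holds in a limited form. The article assigns control of season to a statistic that controls nothing and may not detect it, and it plans comparisons with a phase it calls unmatched.

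**Exposed:** test (i); any uncontrolled contrast with the implementation phase; any level projected from the observation trend, if one is reported; and three-phase comparisons of secondary endpoints without a control series.

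**Not exposed:** the slope contrast in test (iii), under a stable season; and the interactions (ii) and (iiii), under a season shared with the control hospitals.

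The false slope change runs from about 0 to 0.97 days per 26 weeks at the assumed amplitude of 0.2 days, and to twice that at 0.4. Where the slope bias vanishes, phase means differ by about 0.25 days instead (at 0.2). Amplitude, peak week and noise are all assumed, so these figures show how the bias arises and how far it can range; they do not predict this trial's result. The correction is worth making, but it does not undermine the primary estimate.

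**What to change.** 1. Describe Durbin-Watson as a check for residual autocorrelation only, and say what follows if it is positive.
2. Add calendar-month or annual harmonic terms to the ITS, estimated jointly with the control series. The 78 weeks cover only one and a half annual cycles, so the participating hospitals alone identify season weakly.
3. State that study week in the DiD is coded as calendar-week effects shared by both populations, so that the control hospitals absorb common season.
4. Confine hypothesis tests to observation versus intervention or to the controlled contrasts, for secondary endpoints as well. Report the implementation phase descriptively.

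The cost is a change of wording in the analysis plan and some additional parameters. The trade-off is that the implementation phase gets no formal test. No new data collection is needed.
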